## Abstract

**Background:**

The development of suture hole bleeding at peripheral arterial bypass anastomoses using PTFE graft prostheses is a common problem in peripheral vascular surgery. Traditionally the problem is managed by compression with surgical swabs and reversal heparin or by using several haemostatic device (e.g. different forms of collagen, oxidized cellulose, gelatine sponge, ethylcyanoacrylate glue or fibrin) with various success. Preclinical data suggest that the haemostatic effect of collagen is stronger than that of oxidized cellulose, but no direct clinical comparison of their hemostatic performance has been published so far.

**Design:**

This randomized, controlled, prospective trial evaluates the haemostatic effect of Lyostypt versus Surgicel in arterial bypass anastomosis. 28 patients undergoing an elective peripheral vascular reconstruction due to peripheral vascular disease will be included. Suture hole bleeding occurring at the arterial bypass anastomosis using a PTFE prostheses will be stopped by the application of Lyostypt and/or Surgicel. The proximal anastomoses will be randomized intraoperatively. The patients will be allocated into 4 different treatment groups. Group1 Lyostypt distal/Surgicel proximal; Group 2: Lyostypt proximal/Surgicel distal; Group 3: Surgicel distal and proximal; Group 4: Lyostypt distal and proximal. Primary endpoint of the study is time to haemostasis. Secondary endpoints are the number of intraoperatively used haemostatic devices, postoperative mortality within 30 days as well as the intraoperative efficacy rating of the two devices evaluated by the surgeon. As a safety secondary parameter, the local and general complication occurring till 30 ± 10 days postoperatively will also be analysed. After hospital discharge the investigator will examine the enrolled patients again at 30 days after surgery.

**Discussion:**

The COBBANA trial aims to assess, whether the haemostatic effect of Lyostypt is superior to Surgicel in suture hole bleedings of arterial bypass anastomoses.

**Trial registration:**

NCT00837954

## Background

### Rationale

Haemostasis in peripheral vascular surgery is made more difficult by the need for direct arterial and arterial graft suturing as well as by systemic anticoagulation to prevent thrombosis during periods of vascular occlusion. Polytetrafluorethylene (PTFE) is one of the most frequently used graft materials for vascular replacement or bypass in the case when no autologous venae are available [1]. However, the insufficient elasticity of PTFE and its porosity promote the development of suture hole bleeding [2,3] which can cause considerable loss of blood and prolongation of operations due to additional suturing with danger of iatogenic stenosis [2].

There are several medical risk factors that can affect bleeding time and haemostasis, such as hypertension, chronic liver disease, or renal failure [4]. The problem of bleeding from suture holes remains a serious drawback to the use of PTFE. Suture line bleeding in arterial surgery is primarily controlled with precise suture technique, including use of fine suture material and needle [5]. To assist with control of residual bleeding after suturing of arterial operative sites, various topical haemostatic aids are in use. Traditionally the problem of suture hole bleeding is managed by compression with surgical swabs and reversal heparin. Other attempts to control suture hole bleeding have also been used with various success, such as ethylcyanoacyrlate glue [6], different forms of collagen [7-10], oxidized cellulose [9,11], or gelatine sponge [9] or fibrin [12,13]. Another approach to topical haemostasis is the use of an agent that enhances or accelerates formation of autogenous thrombus, such as topical thrombin, which can be used in conjunction with scaffolding-type agents [14,15].

In the COBBANA trial the collagen based haemostat Lyostypt will be compared with Surgicel which is the leading standard and is commonly used for this indication.

### Purpose

This study is designed to demonstrate the superiority of Lyostypt to oxidized cellulose (Surgicel) for haemostasis of suture hole bleeding in arterial bypass anastomoses after vascular reconstruction. Lyostypt is an absorbable, wet stable collagen compress made of collagen fibrils of bovine origin. Collagen leads to thrombocyte adhesion and to activation of coagulation factor XII. Therefore collagen is very effective in haemostasis. Collagen is cell-friendly whereas other haemostats significantly disturb cell growth. Advantages of collagen fleece are fast induction of haemostasis, low tissue reaction and fast absorption [16]. Furthermore, collagen was shown to be the best overall haemostatic agent in microvascular surgery. Authors concluded that collagen fleece establish faster haemostasis than oxidized cellulose and that it was resorbed faster than oxidized cellulose [16].

### Need for the study

The ideal haemostat should be easy to use with good risk-benefit and cost-benefit ratios. Such an agent should be easily applied in a controlled fashion, highly predictable in creating haemostasis, nontoxic and must not have an adverse affect on anastomostic patency, increased anastomotic strength would also be beneficial.

Preclinical data strongly suggest that haemostats made of collagen have a stronger haemostatic effect than haemostats made of oxidized cellulose [16]. While both investigational devices have been in clinical use for many years [7-11], no direct clinical comparison of their haemostatic performance has been published so far.

## Methods/Design

### Objectives of the study

The aim of this study is to evaluate the haemostatic effect of Lyostypt and Surgicel in arterial bypass anastomosis. The measurement of the bleeding time of suture hole bleeding of arterial bypass anastomoses is considered as a suitable efficacy parameter for the assessment of the haemostatic effect. It is expected that the treatment of suture hole bleeding of arterial bypass anastomoses with Lyostypt will reduce the time to haemostasis in comparison to the treatment with Surgicel (primary objective). Local complication and general complication rates occurring till 30 ± 10 days after surgery and handling characteristics of the different devices will also be assessed (secondary objectives).

### Primary endpoint

The primary endpoint of the trial is the time to haemostasis (period from release of the cross-clamping to the moment the wound is completely dry or at least sufficiently dry to finalise the operation without additional measures for haemostasis as judged by the surgeon). If haemostasis is not achieved within 3 minutes, a second equal device is applied for another 2 minutes. If haemostasis is still insufficient, the surgeon will wait for another 5 minutes, before considering other methods. When haemostasis is not achieved after 10 minutes, it is considered a study failure.

### Secondary endpoint

- Local and general complication rate till 30 ± 10 days after surgery

- The number of haemostatic devices used

- Intraoperative efficacy rating of each device, (surgical handling characteristics, tissue adhesion of each device)

- Postoperative mortality until 30 days after surgery

- Recurrence of bleeding at the anastomosis,

- Analysis of adverse events

### Design

This is a randomized, controlled, prospective study to evaluate the haemostatic effect of Lyostypt versus Surgicel in arterial bypass anastomoses.

In this study, 28 eligible patients with a peripheral arterial bypass following peripheral vascular reconstruction, will be treated with the investigational devices during the pilot phase. There will be 4 treatment groups: Group 1 and 2 will receive both products one at the distal and the other at the proximal anastomosis. In group 3 and 4 the same haemostat will be applicated at both anastomoses either Lyostypt or Surgicel. The proximal bypass anastomosis will be randomized for the application of the haemostat. After discharge from the hospital the investigator will examine the patients at 30 ± 10 days after surgery (figure 1 and table 1).

**Table 1 T1:** Flow Chart COBBANA Trial.

	**Visit 1 (Screening)**	**Visit 2 (OP)**	**Visit 3 (2 ± 1 days post OP)**	**Visit 4 (Day of discharge)**	**Visit 5 (30 ± 10 Days post OP)**
Patient information	X				

Informed consent	X				

Demographic data*	X				

Smoker/non-smoker	X				

Inclusion/exclusion	X				

Past medical history	X				

Physical examination	X	X	X 1)	X 1)	X 1)

Surgery		X			

Time to obtain hemostasis		X			

Deviation from surgical procedures as described in the protocol		X			

Number of used devices		X			

Intraoperative handling of the devices		X			

Recurrence of bleeding		X	X	X	x

Adverse Event/Serious Adverse Event		X	X	X	X

Local and general complication/re-operation		X	X	X	X

Mortality					X

* date of birth, gender, weight, height,

1) of the operational wound

**Figure 1 F1:**
[figure not shown]
**COBBANA Trial: Schedule of the visits**. This figure represents a flow chart of all visits conducted in the COBBANA trial. The figure also indicates when the primary and secondary endpoints are collected.

By employing a sequential adaptive statistical design, the results of the pilot phase will be analysed and the appropriate total number of cases determined in a second phase (see section on sample size). If the second phase of this study will be conducted, patients will be recruited and treated as already described for the pilot phase.

### Eligibility

Detailed inclusion and exclusion criteria are specified in table 2. Patients are screened consecutively for eligibility in the participating centre after approval of the study protocol by the local ethics committee. A contract has been signed by Aesculap AG and the participating centre for correct conduction of the trial according to Good Clinical Practice. The participating surgeons performing the intervention have been instructed by detailed manuals.

**Table 2 T2:** Eligibility Criteria.

**INCLUSION CRITERIA**	**EXCLUSION CRITERIA**
• Patients > 18 years	• Emergency surgery
• Informed Consent	• Patients with coagulopathy or uremia
• Indication for a peripheral vascular reconstruction due to peripheral vascular disease	• Participating in another trial with interfering endpoints
• Suture hole bleeding of peripheral arterial bypass anastomosis using PTFE graft	• Patients requiring continuous postoperative anticoagulation
	• Reoperation within one month at the same location
	• Pregnant and breastfeeding women
	• Known or suspected allergies or hypersensitivity to any of the used devices
	• Severe comorbidity (ASA >4)
	• Life expectancy less than 12 months
	• Current immunsuppressive therapy
	• Chemotherapy within last 4 weeks
	• Severe psychiatric or neurologic diseases
	• Lack of compliance
	• Drug- and/alcohol-abuse
	• Inability to understand and to follow the instructions given by the investigator

### Consent

The participating centre recruits trial patients from its patients who are scheduled for an elective implantation of PTFE graft for peripheral revascularization, who develop suture hole bleeding of arterial bypass anastomoses following peripheral vascular reconstruction. All patients who seem to fit to the in- and exclusion criteria will be asked whether they are willing to participate in the COBBANA trial and they will be informed about the purpose of the trial, the operation modalities, data management, and their possibilities and risks. Interested patients will be screened according to inclusion and exclusion criteria and included into the trial after written Informed Consent has been obtained from the patient.

### Randomization

Upon inclusion in the study the patient will receive a unique identification number. Intraoperatively their anastomoses will be randomized to receive either Lyostypt or Surgicel by opening sealed opaque envelopes containing the information which device should be used. The combinations proximal and distal: Lyostypt, proximal: Lyostypt/distal: Surgicel, proximal: Surgicel/distal: Lyostypt, proximal and distal: Surgicel will occur in equal quantities (figure 2).

**Figure 2 F2:**
[figure not shown]
**COBBANA Trial: CONSORT Flow Chart**. Flow Chart of patients according to CONSORT.

The envelopes will be prepared by the sponsor with balanced distribution of either Lyostypt or Surgicel according to a randomization list provided by the statistician. The randomization list is sealed and kept under lock and key until data queries are resolved and the data base is locked. The envelopes will be assigned to the patients in a chronological order. The envelope contains the devices and also two labels with a randomisation number and the information about the device which was applied to the proximal and distal anastomosis, which must be attached to the CRF and the surgery form.

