### Intervention

In the current trial the surgical procedure is standardised to achieve a better comparability of the outcome. For each surgical intervention a Polytetrafluoro-ethylene vascular prostheses from the same manufacture (PTFE prostheses, thin walled, diameters 4-10 mm) will be surgical implanted in accordance with the standard practice of the investigative centre using a non-absorbable polypropylene suture material USP 5-0, USP 6-0 for the anastomotic suture line. The investigator will perform the distal anastomosis first. The clamp will be opened to check for suture hole bleeding. If bleeding occurs, the clamp will be closed and a randomization envelope containing the study material will be opened. The devices will be cut into half. Thereafter, the clamp at the distal anastomosis will be removed and a stopwatch will be started and the randomized device will be placed circumferentially around the anastomosis and applied for three minutes. The suture line is monitored by the investigator and the time required to achieve complete sealing is recorded with a stopwatch. If haemostasis is not achieved after 3 minutes a new equal device is placed around the anastomosis for another 2 minutes and the time to obtain haemostasis is measured with a stopwatch. In the case that suture hole bleeding has not stopped after 5 minutes the investigator will wait for another 5 minutes to achieve haemostasis. Subjects are considered treatment failures if suture hole bleeding could not be controlled within 10 minutes or if additional interventions are required to achieve sealing. Every application of a new device will be recorded with type of device and time after clamp removal.

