### Study Device

The investigational products are the haemostats Lyostypt and Surgicel (= Tabotamp). For Lyostypt, the size 5 cm × 8 cm and for Surgicel, the size 5 cm × 7,5 cm will be supplied to the study centre.

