### Lyostypt

Lyostypt is an absorbable wet-stable collagen compress made of collagen fibrils of bovine origin. Collagen leads to thrombocyte adhesion and to activation of coagulation factor XII. Lyostypt collagen haemostatic fleece is indicated for capillary bleedings, parenchymal haemorrhages, oozing wound haemorrhages, for the local haemostasis in haemodialysis and as a supportive method for other techniques in haemostasis. Lyostypt achieves haemostasis very swiftly, it can be removed easily, it can be applied endoscopically and it can be combined with fibrin glue and antibiotics (16). Collagen haemostats showed low tissue reaction, fast resorption and good biocompatibility (15). Lyostypt is y-sterilized.

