### Surgicel/Tabotamp

Surgicel absorbable haemostat is a sterile absorbable knitted fabric prepared by the controlled oxidation of regenerated cellulose. The fabric is white with a pale yellow cast and has a faint caramel-like aroma. It is strong and can be sutured or cut without fraying. After Surgicel has been saturated with blood, it swells into a brownish or black gelatinous mass which aids in the formation of a clot, thereby serving as a haemostatic adjunct in the control of local haemorrhage. When used properly in minimal amounts Surgicel haemostat is absorbed from sites of implantation with practically no tissue reaction.

Surgicel is used adjunctively in surgical procedures to assist in the control of capillary, venous and small arterial haemorrhage when ligation, suturing or other conventional methods of control are impractical or ineffective.

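### Packing the non-identical devices inside the randomization envelope puts allocation concealment at risk just before the bleeding judgement that decides entry

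*Protocol article*

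**What the plan says.** All references are to the Protocol article.

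- **Concealment.** Under Randomization, anastomoses are randomized during surgery "by opening sealed opaque envelopes containing the information which device should be used".
- **Envelope contents.** The text under Figure 2 in the same section adds: "The envelope contains the devices and also two labels with a randomisation number". The labels also name the device for each site. The sponsor prepares the envelopes from the statistician's list.
- **Order of use.** "The envelopes will be assigned to the patients in a chronological order".
- **Moment of opening.** Under Intervention, the distal clamp is opened to look for bleeding, and then: "If bleeding occurs, the clamp will be closed and a randomization envelope containing the study material will be opened". If the distal site does not bleed, the envelope is opened only when the proximal site is found to bleed.
- **The products.** Study Device: "For Lyostypt, the size 5 cm × 8 cm and for Surgicel, the size 5 cm × 7,5 cm will be supplied". The product sections describe one as a compress, "Lyostypt is an absorbable wet-stable collagen compress made of collagen fibrils of bovine origin", and the other as a fabric, "Surgicel absorbable haemostat is a sterile absorbable knitted fabric prepared by the controlled oxidation of regenerated cellulose".
- **Contents by group.** Under Design: "Group 1 and 2 will receive both products one at the distal and the other at the proximal anastomosis". Groups 3 and 4 receive a single product at both sites.

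**The concern.** An opaque envelope is a sound safeguard when it holds a card. Here it also holds the physical devices, and these are not identical across groups. Opacity does nothing about bulk, stiffness or feel.

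The timing makes this matter. Which envelope comes next is fixed by the order of use. Whether it is opened depends on the surgeon's judgement that a suture hole bleeds, and that judgement comes immediately before opening. A surgeon who had an idea of the contents could, without intending to, call marginal oozing bleeding for one device and not for the other. Easier sites would then collect in one arm.

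This is a different matter from the surgeon knowing the device once it is applied. That knowledge cannot be avoided in this trial; knowledge before entry can be.

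**Working it through.** The plan gives no figure for this point, so the check sets the sections side by side.

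**1. Are the devices in the envelope?** Yes. The text under Figure 2 and the Intervention section both say so. This is a stated procedure, not a detail left out of a condensed article.

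**2. Do the contents differ?** Yes, in product and slightly in size. From the Study Device section:

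- Lyostypt: 5 × 8 = 40 cm²
- Surgicel: 5 × 7.5 = 37.5 cm²
- Difference: 0.5 cm on one side; (40 − 37.5)/37.5 = 6.7% in area

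Thickness, weight and stiffness are not given for either product.

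**3. What could be learned in the worst case?** Suppose, purely as a bound, that the contents could be recognised perfectly from outside. The groups are as defined in the Abstract, and the Randomization section has the four combinations occur equally often.

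| Group | Distal | Proximal | Products inside | Chance that the distal device is Lyostypt, given the contents |
|---|---|---|---|---|
| 1 | Lyostypt | Surgicel | both | 1/2 |
| 2 | Surgicel | Lyostypt | both | 1/2 |
| 3 | Surgicel | Surgicel | Surgicel only | 0 |
| 4 | Lyostypt | Lyostypt | Lyostypt only | 1 |

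Before handling, the chance is 1/2 for every envelope. Perfect recognition leaves it at 1/2 for groups 1 and 2 and settles it for groups 3 and 4. With 28 patients in four equal groups there are 28/4 = 7 per group, so the exposed groups make up 2 × 7 = 14 of 28 envelopes, or half. This is nominal, because the Sample size section lets the number of patients vary until 56 applications have been recorded.

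**4. At which site does it matter?** Only at the first bleeding anastomosis of a patient. Once the envelope is open, its labels show the device for the other site as well. Knowledge at a second bleeding site therefore comes from the opened envelope and not from the packing.

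**5. Could the analysis repair it?** No. Under Statistical Analysis, the unit is the single anastomosis. The model contains the device at that site, the device at the other site, the site, the centre and a subject frailty.

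- None of these terms measures how strongly a site bled before a device was applied.
- A site judged not to bleed receives no randomized device and yields no time to haemostasis, so it never enters the analysis.
- In groups 3 and 4 the device is the same at both sites of a patient, so the comparison between these groups is between patients. The frailty term is taken to be unrelated to treatment, and selective entry would break exactly that assumption.

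**The case against.** A reader might infer that the next allocation can be recognised from outside and that concealment therefore fails. The documents do not support this. The envelopes are sealed and opaque, and the only physical measurement given differs by 0.5 cm on one side. Both products are sterile, so a handler would presumably feel packaging and not the bare device. Inner packs, outer form, storage and custody before opening are not described. A journal article commonly leaves such detail to the full protocol, so its absence is not held against the plan. No section says that anyone handles the envelope before bleeding is checked.

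Three further objections are fair:

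- The two descriptions of the envelope do not contradict each other. The labels inside carry the allocation, so the envelope does contain the information that the Randomization section mentions.
- Groups 1 and 2 could not be separated by feel, so at most half of the envelopes are exposed.
- Any count of selectively entered sites would be invented.

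All of this stands, and it limits the point to a risk of unknown size. It does not remove the point. Placing the devices in the envelope is stated twice, the contents do differ by group, and the two safeguards named, sealing and opacity, do not address bulk or feel.

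**Conclusion.** The point holds as a risk to concealment, not as a demonstrated failure. Non-identical devices are packed in envelopes used in a known order, and each is opened only after a judgement made by the surgeon. The exposure is confined to the first bleeding anastomosis of a patient and falls chiefly between groups 3 and 4, nominally 14 of 28 envelopes. The size of any bias cannot be derived from the documents.

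The conclusion rests on two assumptions: that the packs are not already indistinguishable from outside, and that theatre staff could handle the next envelope before bleeding is judged. The article neither confirms nor excludes either. If the packs are already uniform in outer form and contents, a sentence saying so would settle the matter.

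The change is still worth making, because it is inexpensive and selective entry cannot be corrected afterwards in a small, open comparison whose endpoint is also judged by the surgeon.

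**What to change.** Adopt one of two arrangements, and amend the text under Figure 2 and the Intervention section to match:

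- **Identical packs.** Every pack has the same outer form and the same contents: both products, in the quantity that any group could need, with the allocation card and labels sealed inside. The cost is some unused devices.
- **Card-only envelope.** The sealed opaque envelope holds only the allocation card and the labels, and the devices are supplied separately in theatre. The cost is a check, recorded in theatre, that the device used matches the card, because the physical link between label and device is lost.

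The sponsor already prepares the envelopes, so either option is a matter of repackaging. Neither changes how the devices are applied, and neither changes what the surgeon knows about the second site once the envelope has been opened.

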If haemostasis is achieved at the distal anastomosis the surgeon will perform the proximal anastomosis. Following the anastomotic procedure the clamp at the prosthesis is released. If suture hole bleeding is present, the clamp will be closed. The device according to the randomization procedure will be prepared (if no bleeding at the distal anastomosis had occurred, the randomization envelop has to be opened) and the clamp will be removed and a stopwatch will be started. The randomized device will be placed circumferentially around the proximal anastomosis and applied for three minutes. If haemostasis is not achieved after 3 minutes a new equal device is placed around the anastomosis for another 2 minutes and the time to obtain haemostasis is measured with a stopwatch. In the case that suture hole bleeding has not stopped after 5 minutes the investigator will wait for another 5 minutes to achieve haemostasis. Subjects are considered treatment failures if suture hole bleeding could not be controlled within 10 minutes or if additional interventions are required to achieve sealing. Every application of a new device will be recorded with type of device and time after clamp removal. After achieving haemostasis at the proximal anastomosis the proximal clamp will be removed and the surgical procedure will be finished.

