### Statistical Analysis

The primary criterion is the time to haemostasis at an anastomosis. For the evaluation of the primary criterion, the single anastomosis is treated as the observational unit. Time to haemostasis, which will be censored at 10 minutes, will be included as the response parameter in an accelerated failure time regression model [18] assuming a Weibull distribution for bleeding time with the following explanatory parameters included: treatment on anastomosis (Lyostypt vs. Surgicel), treatment on opposite anastomosis (Lyostypt vs. Surgicel), site of anastomosis (proximal vs. distal), and center. Subject will be included as a shared frailty term with lognormal distribution. The formal null hypothesis to be tested at a level of α = 0.025 (spent over two tests carried out in different stages) is: "Anastomosis bleeding time under Lyostypt is at least as long as under Surgicel".

Haemostasis during 5 and 10 minutes, local and general complication rate till 30 ± 10 days after surgery, the number of used haemostatic devices minus one will be modelled in a logistic mixed regression model using the same covariates as for the main model. Subject will enter the analysis as a random effect. If model instabilities occur due to overspecification (signified by a condition number of the design matrix of more than 40), the term "treatment on opposite anastomosis" and possibly the center effect will be dropped.

The intraoperative efficacy rating scale of each device will be modeled separately for the 4 step ranking scale of adhesion and the 5 step ranking scale of handling, using a logistic mixed model of ordinal responses using the same covariates as in the main model as fixed and surgeon and subject as random effects. Postoperative mortality will be described individually in the final report. Adverse events which are recorded will be reported casuistically, mentioning the haemostypt actually applied at the distal and proximal site.

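### When the distal anastomosis bleeds, the single envelope discloses the proximal device before the surgeon judges whether the proximal anastomosis bleeds and so enters the primary analysis

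*Protocol article*

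**What the plan says.** All references are to the protocol article.

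- **Envelope contents (Randomization, text after Figure 2).** "The envelope contains the devices and also two labels with a randomisation number and the information about the device". The labels cover both sites: "the information about the device which was applied to the proximal and distal anastomosis".
- **Order of surgery (Intervention).** "The investigator will perform the distal anastomosis first".
- **Opening at the distal step (Intervention).** "If bleeding occurs, the clamp will be closed and a randomization envelope containing the study material will be opened".
- **Proximal step (Intervention).** "If haemostasis is achieved at the distal anastomosis the surgeon will perform the proximal anastomosis". After clamp release the surgeon looks for bleeding: "If suture hole bleeding is present, the clamp will be closed". Only then is the allocated device prepared, the clamp removed and the stopwatch started.
- **No second envelope (Intervention).** The envelope is opened at the proximal step only in one case: "if no bleeding at the distal anastomosis had occurred, the randomization envelop has to be opened".
- **Analysis unit (Statistical Analysis).** "the single anastomosis is treated as the observational unit".
- **Accrual (Sample size).** Stage 1 runs until 56 applications of a randomised device have been recorded. It is planned as 28 patients, the exact number depending on how many anastomoses bleed.
- **Endpoint (Primary endpoint).** Haemostasis is judged by the surgeon.

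**The concern.** At the distal site the order is sound: bleeding is seen first and the allocation is learned afterwards. At the proximal site, in any patient whose distal site bled, the order is reversed. The surgeon knows the proximal device while sewing that anastomosis and while deciding whether it bleeds. That decision determines whether the site contributes to the primary analysis at all.

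If borderline oozing were called bleeding more readily with one device than with the other, the proximal units in the two arms would no longer be comparable. Leaving out mild bleeds in one arm makes that arm look slower. The planned model adjusts for treatment, opposite treatment, site, centre and subject frailty. None of these can restore a unit for which no time was recorded. The stated one-sided level of 2.5% assumes that no such selection takes place.

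**Working it through.** **1. The plan's own error rate.** For the two-stage product test with α₁ = 0.0102, futility bound 0.50 and constant 0.00380 (Sample size):

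α = α₁ + c·ln(α₀/α₁) = 0.0102 + 0.0038 × ln(0.50/0.0102) = 0.02499, which rounds to 0.025.

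The stated level is arithmetically right. It does not cover selection into the analysis.

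**2. Order of events at each site.**

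| Step | Distal bled | Distal did not bleed |
|---|---|---|
| Distal bleeding judged | allocation unknown | allocation unknown |
| Envelope opened | now; both devices disclosed | not yet |
| Proximal anastomosis sewn | proximal device known | allocation unknown |
| Proximal bleeding judged | proximal device known | allocation unknown |
| Proximal device applied and timed | only if judged to bleed | only if judged to bleed (envelope opened first) |

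The problem lies in the left-hand column only.

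**3. Does a non-bleeding site leave the analysis?** The article does not say so in as many words. It follows from Intervention (no bleeding, so no device and no stopwatch) and from Sample size (accrual counts applications).

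**4. Reach.** 56 applications / 28 patients = 2.0 per patient, so the plan expects both sites to bleed in essentially every patient. The left-hand column is then the normal path, and up to 28 of 56 stage-1 units (50%) are affected. If distal sites bleed less often, the share is smaller.

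**5. Illustrative size.** The article gives no effect size, Weibull shape or frailty variance, so these inputs are assumptions: no true effect, 28 patients in four equal groups, Weibull scale 4 minutes, log-time scale 0.7, subject frailty SD 0.5 on the log scale, and censoring at 10 minutes. The fitted model is Weibull without a frailty term. The mildest fraction f of Surgicel proximal bleeds goes undeclared. With 14 such sites, f = 10% is 1.4 sites and f = 20% is 2.8 sites.

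| Selection on | f = 10%: time ratio | f = 20%: time ratio |
|---|---|---|
| the eventual time itself (worst case) | 0.95 (about 5% faster) | 0.92 (about 8% faster) |
| visible severity, correlation 0.5 with log time | 0.97 (about 3% faster) | 0.95 (about 5% faster) |

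In the worst case, rejection at the stage-1 level of 0.0102 rises from about 1.6% with no selection to about 3% (f = 10%) or 4% (f = 20%). The 1.6% exceeds the nominal 1.02% because the fitted model leaves out the frailty, so only the rise is informative. With 4,000 simulated trials, the simulation standard error near 4% is √(0.04 × 0.96/4000) = 0.3 percentage points.

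**6. Second model.** With exponential times (scale 4 minutes), the same frailty SD and censoring, and a simple rate-ratio test, the apparent haemostasis rate ratio favouring Lyostypt is 1.00, 1.06 and 1.12 for f = 0, 10% and 20%. Rejection at 0.0102 is 1.8%, 2.3% and 3.2%. The direction is the same and the rise somewhat smaller. Selection against Lyostypt would produce the mirror image and could hide a real benefit.

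**The case against.** Several points can fairly be made for the plan.

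- **Concealment.** A reader might infer that allocation concealment fails altogether. The article does not support that. The envelopes are sealed and opaque, and each stays closed until the patient's first bleeding site has been seen. What is exposed is the later entry of the second site.
- **Proof of bias.** A reader might infer that the primary result will be biased. The article shows an opportunity only, and the direction is unknown. The surgical procedure is standardised, and nothing suggests that surgeons would sew or judge differently by device.
- **Size.** A linear model on uncensored log times gives much larger figures for the same scenario (11% and 17% faster). That is not the planned model. Log-Weibull times have a long left tail, so a linear fit is unusually sensitive to removing the shortest times. The figures above use a Weibull model with the planned 10-minute censoring. Even then, selection on the eventual time assumes foresight that the surgeon does not have at clamp release.
- **Internal tension.** The 50% reach needs nearly every site to bleed, which leaves little room to call 10% or 20% of one arm's proximal sites dry. If many sites do not bleed, fewer units are exposed. The reach and the larger selection fractions should not both be taken at their maximum.
- **Larger exposure elsewhere.** The surgeon also judges the endpoint knowing the device, and separate packs do not change that.

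All five stand as limits on the size and wording of the point. None removes it. The envelope contents and the opening order are stated explicitly, so this is a procedure fixed in the plan and not a detail lost in condensing the protocol. Unblinded endpoint assessment may be hard to avoid with these devices, but unblinded entry is easy to avoid.

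**Conclusion.** The point holds as a risk of selection bias after randomisation. In patients whose distal site bled, entry of the proximal anastomosis into the primary analysis is judged with its device known. By the plan's own count this affects up to 28 of 56 stage-1 units. The planned covariates cannot correct it.

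The plausible size is modest. Under the stated assumptions the apparent advantage is about 3% to 8% in time to haemostasis if 10% to 20% of one arm's proximal bleeds go undeclared. In the worst case, stage-1 rejection under no effect roughly doubles or somewhat more (about 1.6% to 3% or 4%). The stage-1 figure is not the overall error rate of the two-stage design, which was not simulated. The direction cannot be known from the article.

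This should be fixed because the remedy is cheap. It does not invalidate the design.

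**What to change.** For every envelope not yet used, including those for any second stage, replace the single envelope with two sealed packs per patient, one distal and one proximal. Draw them from the same list with the same four combinations in equal quantities. Open each pack only after bleeding at that site has been confirmed and written on the surgery form. With four equal combinations, knowing the distal device leaves the proximal device at even odds, so the second pack remains concealed.

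For patients already treated under the single envelope, report the proximal bleeding rate by allocated device, so that readers can see whether entry differed between arms.

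The cost is repacking and a revised instruction to surgeons. No extra patients, staff or surgical steps are needed, and the sample size and analysis model stay as they are. Recruitment had already begun (Current status and duration of the trial), so the change would fall within stage 1 and should be documented as such. The surgeon's unblinded judgement of haemostasis would remain.
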